Neurofeedback based on real-time functional magnetic resonance imaging (rt-fMRI) uses measured changes in brain activation to help participants regulate activity in selected regions or networks. During rt-fMRI neurofeedback, participants are provided with visually presented brain network activation information in real time (24). The rt-fMRI neurofeedback targeting the brain areas within SN involved in emotion processing (e.g., amygdala, insula, and striatum) decreased the anhedonic or depressive scores (25, 26). However, the effects of rt-fMRI neurofeedback (NF) based on CEN-SN on anhedonia to the best of our knowledge have not been investigated previously. Network-based NF can be used to recalibrate the balance between brain networks (27). It has been recommended that researchers use NF methods that consider neural response across regions (i.e., functional connectivity) (28). Recent studies have found that participants can flexibly regulate the balance between the CEN and SN through rt-fMRI neurofeedback which could promote resilience to stress (29). Therefore, the use of rt-fMRI neurofeedback to improve goal-directed reward learning is a potential intervention that involves the interaction between CEN and SN. Additionally, reward learning studies have typically adopted computational modeling during behavioral tasks to estimate expected value and reward prediction errors (RPEs) (20). Therefore, the current study was designed to adopt reward learning tasks (30) and computational modeling in anhedonic individuals to examine goal-directed brain network dynamics. Network-based rt-fMRI neurofeedback will be utilized to improve the balance of CEN/SN within the goal-directed brain network (Figure 1). The within-group changes of depressive symptoms after rt-fMRI NF training of goal-directed brain network will be examined to assess the effects of rt-fMRI NF intervention to improve depressive and/or anhedonic symptoms for depressed patients. The goal-directed RL, as well as CEN/SN changes (CEN-SN functional connectivity) at 3- and 6-month follow-ups, will also be examined to evaluate the long-term rt-fMRI neurofeedback training effects. This study may provide evidence to elucidate the effect of rt-fMRI NF based on the goal-directed system in alleviating depressive/anhedonic symptoms. The rt-fMRI NF training may have clinical implications with improved safety and minor side effects (31).

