## Methods and analysis

### Aim

To determine whether rt-fMRI neurofeedback of the goal-directed system could improve the depressive and/or anhedonic symptoms of depressed patients after training and at follow-ups;To examine the short-term and long-term effects of rt-rMRI neurofeedback on the goal-directed RL behavioral and/or connectivity imaging mediators.

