### Procedure

This study is a double-blind randomized yoke-controlled rt-fMRI NF experiment, with follow-up assessments at 3 and 6 months after rt-fMRI NF (Figure 2). Participants will be randomly assigned to the experimental group (NF/YC) and given random numbers by a third party, who encodes the intervention with matching random numbers. The experimenter who will rate the outcome and/or analyze the data will be blind to group assignment. The CRED-NF checklist indicating which analyses will be performed and listed as supplementary material (available on the Open Science Framework preregistration, https://osf.io/ec396; CRED-NF checklist, https://osf.io/8wcqt).

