#### Pre- and post-test

Before and after the neurofeedback intervention, the primary and secondary outcome measures of the depressive and anhedonic symptoms will be assessed in all subjects. The behavioral tasks will be repeated post-training to evaluate the NF training effect on goal-directed behavior. The follow-up assessments include the primary outcome of depression and secondary outcome of anhedonia, the goal-directed RL (model-based weighting parameter ω), and the CEN-SN functional connectivity (Pearson's correlation) based on prediction errors (PEs) (Figure 2).

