#### Real-time fMRI neurofeedback of individual goal-directed system in anhedonic depression

The anhedonic depressed participants (*n* = 40) will be randomized into the neurofeedback (NF) group (*n* = 20) and the yoke control (YC) group (*n* = 20). We used blocked randomization to form the allocation list (1:1 ratio) for the two comparison groups (NF and YC), by using a computer random number generator to select random permuted blocks (size = 10). The NF group will receive rt-fMRI neurofeedback intervention, with ~60 min per session, once per week for a total of four sessions. Participants in the YC group who are paired with one specific participant from the NF group will receive feedback signals from that participant during the same run. Thus, for the YC group, the sham rt-fMRI signals will not be corresponding to the participant's brain activity. The healthy control (HC) group (*n* = 20) will receive no intervention.

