##### Sample size

The sample size is determined based on a heuristic justification (36) according to median recruits (*n* = 18) of fMRI neurofeedback (37). Moreover, given that this is a feasibility study with constraints on limited resources, a power calculation is not necessary according to the reporting and experimental design consensus in the NF field (38).

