##### Self-regulation performance

For each subject in the patient group in each session, self-regulation performance will be assessed with the CEN-SN activation difference (computed through online time courses of ROIs extracted using Turbo-BrainVoyager) during the training. Self-regulation performance will be defined as the mean % signal change of ROIs (CEN and SN) over all the NF runs. The self-regulation performance will then be submitted to an ANOVA with the factors group (NF vs. YC) and session (four sessions) for the group and/or time effects of rt-fMRI NF training.

Additionally, to investigate the pre- and post-training difference in CEN-SN functional connectivity for each patient group, we will apply the paired *t*-tests or Wilcoxon signed-rank tests (depending on parametric or non-parametric distributions) between the pre- and post-training tests, while undergoing MDT behavioral task during neuroimaging.

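### CEN–SN functional connectivity is tested only before versus after within each arm, and ω has no stated NF-versus-YC comparison, so the neurofeedback effect that the second aim seeks on these two measures is not estimated from the randomisation

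*Protocol article*

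**What the plan says.** The Aim section gives as its second objective "To examine the short-term and long-term effects of rt-rMRI neurofeedback on the goal-directed RL behavioral and/or connectivity imaging mediators". The Procedure section describes the design: "This study is a double-blind randomized yoke-controlled rt-fMRI NF experiment". The section on the neurofeedback intervention randomises 40 patients 1:1, 20 to NF and 20 to YC. Healthy controls receive no intervention.

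Under Pre- and post-test the purpose is causal: "The behavioral tasks will be repeated post-training to evaluate the NF training effect on goal-directed behavior". The same section schedules ω and CEN–SN functional connectivity, defined as a Pearson correlation, at follow-up. The Introduction says that both will be examined at 3 and 6 months to judge long-term training effects.

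The stated analyses are:

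- **Functional connectivity (Self-regulation performance):** paired t or Wilcoxon signed-rank tests, "to investigate the pre- and post-training difference in CEN-SN functional connectivity for each patient group".
- **Choice behaviour (Behavioral data):** a mixed model whose only group factor is anhedonic patients versus healthy controls.
- **Mediators (GD-RL behavioral and connectivity imaging indicators):** an exploratory within-group regression using ω and the CEN–SN activation difference.
- **Symptoms (Intervention effect analysis):** a Bayesian ANCOVA of NF versus YC adjusted for baseline, for HAMD-17 and SHAPS, after training and at both follow-ups.
- **Training signal (Self-regulation performance):** an ANOVA of the CEN–SN activation difference with group (NF, YC) and session as factors.

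The Introduction also describes the symptom analysis as a within-arm one: "The within-group changes of depressive symptoms after rt-fMRI NF training of goal-directed brain network will be examined to assess the effects".

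**The concern.** In a yoke-controlled randomised trial, the effect of neurofeedback is the difference between NF and YC. A change within the NF arm also contains task practice, placebo response and natural change. The Discussion names these non-specific influences itself and gives them as background to adopting the yoked design. Testing each arm against its own baseline sets that control aside.

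The usual error follows when one arm reaches significance, the other does not, and the contrast is read as an effect. Two separate p-values do not test the difference between arms. For ω, none of the stated analyses contains an NF/YC term, so the article gives no route from the data to the effect that the aim names. What is at stake is the mechanistic conclusion: whether neurofeedback changed goal-directed learning or network coupling, in the short or the long term.

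**Working it through.** **Which measures get a randomised comparison**

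| Measure | Analysis stated | NF vs YC? |
|---|---|---|
| HAMD-17, SHAPS (post, 3 and 6 months) | Bayesian ANCOVA, baseline-adjusted | Yes |
| CEN–SN activation difference in the four training sessions | group × session ANOVA | Yes |
| CEN–SN functional connectivity during the task, pre to post | paired test in each arm | No |
| CEN–SN functional connectivity, 3 and 6 months | scheduled; no analysis stated | No |
| ω, post, 3 and 6 months | within-group exploratory mediator only | No |

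The mixed model for choices cannot fill the gap, because its group factor sets patients against untreated healthy controls. The mediator regression cannot either: a model fitted within one arm has no path from treatment assignment to the mediator.

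**How often separate tests mislead**

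The article gives no figure to reproduce. Its sample size is heuristic, and it holds that "a power calculation is not necessary according to the reporting and experimental design consensus in the NF field".

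Inputs from the article: 20 per arm; paired tests. Assumptions, none of them stated there: paired t-test at two-sided 5%; independent arms; no dropout; the same true standardised pre–post change (dz) in both arms, so no NF effect.

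1. Power in one arm: p = P(|T| > t₀.₉₇₅,₁₉), with T noncentral t on 19 df and noncentrality dz × √20.
2. NF significant and YC not: p(1 − p).
3. Exactly one arm significant, in either direction: 2p(1 − p).

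Example at dz = 0.5: p = 0.565; 0.565 × 0.435 = 0.246; doubled, 0.492.

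| dz | p | NF only | exactly one arm |
|---|---|---|---|
| 0 | 0.050 | 0.048 | 0.095 |
| 0.2 | 0.136 | 0.117 | 0.235 |
| 0.3 | 0.247 | 0.186 | 0.372 |
| 0.4 | 0.397 | 0.239 | 0.479 |
| 0.5 | 0.565 | 0.246 | 0.492 |
| 0.6 | 0.721 | 0.201 | 0.402 |
| 0.8 | 0.924 | 0.070 | 0.141 |
| 1.0 | 0.989 | 0.011 | 0.023 |

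The NF-only column cannot exceed 0.25, its value at p = 0.5. Simulation with 100,000 replicates agrees: 0.048, 0.187, 0.250 and 0.200 at dz 0, 0.3, 0.44 and 0.6. In the same simulations a direct two-sample t-test of the changes was falsely significant in 0.050 to 0.051 of trials, whatever the common change.

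**What the direct comparison can detect**

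With 20 per arm and 38 df, the noncentrality is d × √(20/2), where d is the difference in SD-of-change units. Power is 0.15 at d = 0.3, 0.34 at 0.5 and 0.69 at 0.8; 80% power needs d of about 0.91. Baseline adjustment may improve this, by an amount that the article does not allow to be computed.

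**The case against.** Four points weigh on the other side.

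*One imaging measure is compared between arms.* The group × session ANOVA is a randomised comparison, and the mediator section classes the CEN–SN activation difference as a connectivity indicator. The aim is also worded as and/or. A reader might infer that the second aim has no randomised comparison at all; that is not supported. The ANOVA does not close the gap, however. It concerns the regulated signal during training, whereas Pre- and post-test defines functional connectivity as a correlation, and ω is not in it.

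*The ω and follow-up parts are omissions from an article.* A preregistration and a reporting checklist are cited and not shown, and they may contain an arm comparison. The patient-versus-control model also serves a different objective. This carries weight for ω, and the point is correspondingly milder there. It does not apply to the connectivity tests or the mediator analysis, whose within-arm form the article fixes.

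*The measures are mechanistic.* The primary and secondary outcomes are compared NF versus YC with baseline adjustment, and the article calls this a feasibility study. This stands. A reader might infer from the Introduction's wording that symptoms too will be judged within arms, but the Intervention effect analysis is the operative text and is clear.

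*The percentages depend on assumptions.* They do, and they peak in the middle of the dz range. The 37–49% for exactly one significant arm (dz 0.3–0.6) might be read as a false-claim rate. It is not: half of it is the reverse pattern, and the article states no rule that infers an effect from one significant arm.

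**Conclusion.** The point holds for two measures: task-based CEN–SN functional connectivity after training and at follow-up, and ω at all times after baseline. For these, the analyses stated in the article give no randomised estimate of the neurofeedback effect.

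If the within-arm tests were read as evidence of an effect, the misleading NF-only pattern would occur in about 19–25% of trials for dz between 0.3 and 0.6, and less often outside that range. A direct two-sided test errs in 5% in total, both directions together. These figures rest on the assumed 5% level, equal true change, independent arms and full follow-up. The underlying argument, that two within-arm tests do not test the difference between arms, needs none of these.

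This should be corrected before analysis, but it does not threaten the main efficacy conclusion on HAMD-17 and SHAPS.

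**What to change.** - Apply the NF-versus-YC ANCOVA already specified for symptoms to ω and to CEN–SN functional connectivity, after training and at 3 and 6 months. Adjust each for its own baseline, and report NF minus YC with an interval.
- Keep the paired within-arm tests as description only, and say so.
- Align the Introduction's wording on within-arm symptom change with the between-arm comparison in Intervention effect analysis.
- Label the ω and connectivity results as mechanistic. With 20 per arm, a non-significant difference should not be read as absence of effect.

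The cost is analysis work and a few sentences. Both measures are already scheduled before and after training and at follow-up, and the Participants section says that recruitment had not begun at submission, so no visit, scan or task needs to be added.

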#### Intervention effect analysis

##### Primary and secondary outcomes

We will examine the difference in depressive symptoms between the NF and YC groups at the post-test after the training. Bayesian ANCOVA with the group as a fixed factor and the baseline HAMD scores as covariates will be used, using the default JASP (https://jasp-stats.org/) multivariate Cauchy priors (44), and the statistical approach has been described previously (25). The advantage of ANCOVA over repeated-measures (RM) models has been mentioned elsewhere (45). The additional covariates include age, gender, and duration of illness. The dependent variable will be post-test HAMD scores. Similar analyses will be performed on the anhedonic symptoms (SHAPS), with the same covariates and dependent variable. Additionally, similar analyses will also be performed on the primary and secondary outcomes at 3- and 6-month follow-ups.

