##### Primary and secondary outcome measures

Primary outcome measures: HAMD-17 (33). The severity of depressive symptoms will be assessed using the total score of HAMD-17. The higher the score, the more severe the depressive symptoms.

Secondary outcome measures: Snaith–Hamilton Pleasure Scale (SHAPS) (34). The scale includes four aspects of interest/entertainment, social interaction, sensory experience, and food/drink, and has a total score of 14 to 56. It has good validity and reliability to evaluate the hedonic experience of adult outpatients with MDD (35).

The changes in depression and anhedonia symptoms will be assessed using HAMD-17 and SHAPS before and after the NF intervention, respectively. Follow-up assessments of depression (HAMD) and anhedonia (SHAPS) symptoms will be conducted at 3 and 6 months after the intervention.

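### The SHAPS analysis carries over the HAMD model's covariates and dependent variable, so as written it adjusts anhedonia for baseline HAMD instead of baseline SHAPS

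*Protocol article*

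**What the plan says.** All the model statements are in the Protocol article, Intervention effect analysis, under Primary and secondary outcomes.

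- Model and baseline covariate: "Bayesian ANCOVA with the group as a fixed factor and the baseline HAMD scores as covariates will be used".
- Other covariates: "The additional covariates include age, gender, and duration of illness".
- Outcome in the model: "The dependent variable will be post-test HAMD scores".
- SHAPS: "Similar analyses will be performed on the anhedonic symptoms (SHAPS), with the same covariates and dependent variable".
- Follow-up: "similar analyses will also be performed on the primary and secondary outcomes at 3- and 6-month follow-ups".

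The section Primary and secondary outcome measures makes HAMD-17 primary and SHAPS secondary, and provides for SHAPS before training, after training and at 3 and 6 months: "The changes in depression and anhedonia symptoms will be assessed using HAMD-17 and SHAPS before and after the NF intervention, respectively". A baseline SHAPS score will therefore exist for each participant assessed as planned.

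**The concern.** The covariate list has just been fixed as baseline HAMD, age, gender and duration of illness, and the dependent variable as post-test HAMD. Carrying both over unchanged leaves the SHAPS analysis without its own baseline and, on the words alone, without its own outcome. Baseline SHAPS is not named as a covariate anywhere in the article.

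This is not a detail left for an analysis plan to fill in. Had the article said only that SHAPS would be analysed similarly, a reader could supply the matching baseline. It adds an explicit rule instead. A later plan would have to repeat that rule or contradict the published protocol, and until then the choice of baseline adjustment is open.

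SHAPS is the only anhedonia measure among the listed outcomes, anhedonic symptoms are named in the first aim, and patients are selected for high anhedonia. The section also prefers ANCOVA over repeated-measures models. Much of what ANCOVA gains comes from adjusting for the outcome's own baseline, and in a trial with 20 patients per arm that gain is worth keeping.

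**Working it through.** **1. The wording.** The article gives no figure to reproduce, so the first check sets out what the text specifies.

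| Element | HAMD model, as stated | SHAPS model, literal | SHAPS model, dependent variable read as SHAPS |
|---|---|---|---|
| Dependent variable | post-test HAMD | post-test HAMD | post-test SHAPS |
| Baseline covariate | baseline HAMD | baseline HAMD | baseline HAMD |
| Other covariates | age, gender, duration | the same | the same |

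The literal column duplicates the primary model and contains no SHAPS term, which conflicts with the opening of the same sentence. The last column resolves that conflict but still has the wrong baseline.

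**2. The cost of the wrong baseline.** Let r_S be the correlation of baseline with post-test SHAPS, and r_H that of baseline HAMD with post-test SHAPS. The article gives neither, so both are assumptions: r_S 0.5–0.7 and r_H 0.2–0.3. Age, gender and duration are taken not to alter the comparison. With the post-test SHAPS variance set to 1, the residual variance is 1 − r² for the baseline used, and the ratio is (1 − r_S²)/(1 − r_H²).

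| r_S | r_H | 1 − r_S² | 1 − r_H² | Ratio | Inverse |
|---|---|---|---|---|---|
| 0.5 | 0.2 | 0.75 | 0.96 | 0.781 | 1.28 |
| 0.5 | 0.3 | 0.75 | 0.91 | 0.824 | 1.21 |
| 0.7 | 0.2 | 0.51 | 0.96 | 0.531 | 1.88 |
| 0.7 | 0.3 | 0.51 | 0.91 | 0.560 | 1.78 |

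The four corners span 0.53–0.82. The inverse, 1.21–1.88, says that the HAMD-adjusted analysis would need about 21–88% more patients for the same precision.

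**3. Wider assumptions.** Take r_S 0.3–0.7 and r_H 0.1–0.4, keeping pairs in which the SHAPS baseline is the better predictor. On the grid tried, the inverse ratio runs from 0.96/0.91 = 1.05 (r_S 0.3, r_H 0.2) to 0.99/0.51 = 1.94 (r_S 0.7, r_H 0.1). At the low end almost nothing is lost.

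**4. On the scale of the trial.** With 20 per arm, two-sided 0.05 and 80% power (assumed yardsticks; the planned analysis is Bayesian), the detectable difference by normal approximation is (1.960 + 0.842) × √(2/20) × √(1 − r²) = 0.886 × √(1 − r²) SD.

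- SHAPS baseline, r_S = 0.5: 0.886 × 0.866 = 0.77 SD.
- HAMD baseline, r_H = 0.2: 0.886 × 0.980 = 0.87 SD.

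For an assumed true difference of 0.8 SD, power is 83% against 73%.

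**5. Chance imbalance.** The standard error of the difference in baseline SHAPS between arms is √(2/20) = 0.32 SD. An imbalance of that size, wholly unadjusted, shifts the estimate by 0.32 × 0.5 to 0.32 × 0.7, about 0.16–0.22 SD. Adjusting for a correlated HAMD baseline would remove part of it. This is another view of the loss in step 2, not an additional harm.

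**The case against.** The strongest reply is that the sentence is loose but its intent is clear: the same structure, with SHAPS in place of HAMD throughout. Three things support this. The sentence says the analyses are of SHAPS. The section covers both outcomes. And the follow-up sentence asks only for similar analyses, where the dependent variable has to change with the visit, so some substitution is evidently allowed.

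For the dependent variable this reply succeeds. A reader might infer that SHAPS will never be analysed; the article does not support that, because the sentence itself makes SHAPS the object of the analysis. For the covariates it succeeds less well. The text says the covariates are the same, and baseline HAMD is one of them. Reading that as the corresponding baseline is possible, but the words do not say it.

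A reader might also infer that the 3- and 6-month SHAPS analyses are bound to the same rule. The rule is not repeated for those visits, so their baseline is unclear rather than fixed wrongly.

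It is also fair to say that the article calls this a feasibility study, sets no power target and concedes that power may be insufficient. An equivalent in extra patients therefore describes relative information, not a missed target.

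**Conclusion.** The point stands as a misstated covariate rule for a secondary outcome, with a self-contradictory dependent variable that is probably a drafting slip. Its weight is moderate.

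The cost is precision. Under the assumed correlations of 0.5–0.7 and 0.2–0.3, residual variance with the SHAPS baseline is about 53–82% of that with the HAMD baseline. None of these correlations comes from the article, and with weaker ones the loss could be close to zero.

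A reader might infer that the SHAPS comparison would be biased. It would not be: patients are allocated 1:1 at random, so adjusting for a different baseline leaves the comparison free of systematic bias. The primary post-test HAMD analysis uses its own baseline and is unaffected.

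**What to change.** Replace the SHAPS sentence with: *For SHAPS, the dependent variable is the SHAPS score at the given visit (post-test, 3 months, 6 months) and the covariates are baseline SHAPS, age, gender and duration of illness.* Naming the three visits also settles the follow-up analyses.

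The cost is one sentence. No new data are needed, because SHAPS is already to be assessed before training. The change should be made before unblinding, so that the baseline adjustment is not chosen with the results in view.
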